### Statistical analyses

All variables will be presented using descriptive statistics (frequencies, percentages, means/standard deviations, medians/interquartile ranges, and various graphical representations). Point estimates will be accompanied by confidence intervals.

The design for the endpoints of primary objective 1 is based on a method of fixed a priori ordered hypotheses [41]. Thus, the second primary endpoint will be analysed only confirmatory at an α of 5% if the null hypothesis of the first primary endpoint can be rejected (*p* < 0.05). This design assures a global alpha of 0.05. The analyses of the primary endpoints (including both the first and second primary endpoints) will be conducted using the Χ^2^-test of independence, setting the level of statistical significance at *p* < 0.05.

Additionally, a multivariable regression analysis in the sense of a sensitivity analysis is planned to adjust for potential risk factors. It is not planned to use imputation to handle missing data in the primary analysis. However, missing data will be accounted for in sensitivity analyses using the following methods: imputation of the last available QoL measurement (last observation carried forward (LOCF) approach); definition of patients with missing data as nonresponders. Analyses will be performed in the intention-to-treat population (sensitivity analysis in the per-protocol population). Statistical tests regarding the secondary endpoints will also use the *p* < 0.05 significance threshold, but all secondary results will be interpreted in an explanatory manner. Secondary analyses will include analyses of covariance (ANCOVAs) using the continuous QoL data as the dependent variable and sex, age, study region, and baseline QoL as covariates.

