### Measures

#### Quality of life (patient)

QoL is measured by using the validated QoL questionnaires of the European Organisation for Research and Treatment of Cancer (EORTC), consisting of a core module (EORTC QLQ-C30 [30]) and a module for lung cancer patients (EORTC QLQ-LC29 [32]). The questionnaire is a self-administered instrument with a multidimensional structure measuring QoL on a four-point Likert scale or rather on a seven-point Likert scale for the global QoL dimension. Satisfactory internal consistency, good retest-reliability, and good construct and clinical validity have been demonstrated [30, 32]. For every dimension scores are uniformly transferred to a scale from 0 (= very bad QoL) to 100 (= very good QoL). A cut-off score < 50 points indicates a need for QoL therapy in each QoL dimension [6–9]. This decision criterion was chosen because the present study aims to highlight the patient’s perspective of subjective impairment. This is operationalised by dichotomising symptom scores with a majority of “quite a bit” and “very much” responses to the “bad” side of the spectrum (< 50) and “not at all” and “a little” responses to the “good” side (≥ 50). For outcome measurement, eight scales have been selected according to the results of both previous RCTs (9; 8) and our preliminary study examining patient and physician preferences: global QoL, shortness of breath, physical functioning, social functioning, fear of progression, emotional functioning, pain, and financial situation (Fig. 4).

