### Primary and secondary outcomes

Concerning primary objective 1, two endpoints will be analysed. The first endpoint is binary: Treatment is defined as successful (responder) if all eight dimensions of the QoL profile reach a value of ≥ 50 points 6 months after baseline (0 = very bad; 100 = very good). If the value of at least one QoL dimension is < 50 points, the treatment is considered unsuccessful (nonresponder), as substantial restrictions in even one QoL dimension can have a negative impact on a patient's overall QoL. As lung cancer is a serious disease with a short median survival time of approximately one year, QoL at 6 months after baseline was chosen as the timepoint to assess the primary endpoint [2, 39, 40]. We expect this period to be long enough to reveal significant effects of the investigated QoL intervention. The second endpoint, enhancing the credibility of the first primary endpoint, are the rates of patients with a QoL score ≥ 50 points separate for each dimension of the QoL profile 6 months after baseline. Both endpoints formulated above will be tested in strict order (1), (2); that is, a statistical testing procedure with a priori ordered hypotheses will be applied [41].

Concerning primary objective 2, QoL data will be supplemented with clinical cancer registry data to answer relevant medical and therapeutic questions. More research questions will be defined in two workshops using a nominal group technique with a group size of 7 to 15 participants (physicians, patients) [42].

Concerning secondary objectives 3–6, a variety of items concerning the perception of the QoL monitoring system will be analysed exploratively.

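### Step 2 of the ordered test procedure holds eight unadjusted 5% tests, so the two-step order does not assure a global alpha of 0.05

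*Protocol article*

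**What the plan says.** - **Primary and secondary outcomes.** The first endpoint is binary: a patient is a responder if all eight dimensions score at least 50 at 6 months. The second endpoints "are the rates of patients with a QoL score ≥ 50 points separate for each dimension of the QoL profile 6 months after baseline". Only two levels are ordered, (1) and then (2).
- **Quality of life (patient).** "For outcome measurement, eight scales have been selected". The eight named there are "global QoL, shortness of breath, physical functioning, social functioning, fear of progression, emotional functioning, pain, and financial situation".
- **Statistical analyses.** The gate reads "the second primary endpoint will be analysed only confirmatory at an α of 5% if the null hypothesis of the first primary endpoint can be" (the sentence closes with rejection at p < 0.05). On the method, the article says "The analyses of the primary endpoints (including both the first and second primary endpoints) will be conducted using the Χ^2^-test of independence". The threshold given for both endpoints carries no adjustment: "setting the level of statistical significance at *p* < 0.05". Between the gate and the method stands the claim at issue: "This design assures a global alpha of 0.05".

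The article gives no order among the eight dimensions, no split of alpha, no rule that all eight must be significant, and no single global test for step 2.

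**The concern.** Hierarchical testing works because a false rejection at one step can occur only after a true rejection, or a 5% error, at the step before. That argument needs each step to spend at most 5%. Here step 1 is one hypothesis, but step 2 is eight, each tested at the full 5%.

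The order protects the family when the first null hypothesis is true. It does not protect it when the composite really improves and some dimensions do not. That is a natural way for this trial to succeed, because the eight scales range from pain to financial situation and the intervention need not move all of them.

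At stake are the dimension-level results, which the plan makes confirmatory. A reader would take them as proof of which areas of quality of life the monitoring system improves.

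**Working it through.** **Inputs from the article.** Rates of 25% and 45% for the first endpoint, α = 5%, 80% power, 89 per group (Sample size); eight dimensions; chi-square at p < 0.05 for both endpoints. Sidedness is not stated and is taken as two-sided.

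**1. The plan's own sample size.** With pooled rate 0.35:

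n = [1.96·√(2·0.35·0.65) + 0.8416·√(0.25·0.75 + 0.45·0.55)]² / 0.20² = (1.322 + 0.555)² / 0.04 ≈ 88.1, so 89 per group.

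The stated figure reproduces (power at 89: 80.4%). A one-sided test would give 70. The calculation covers the first endpoint only.

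**2. Error within step 2 once it is reached.** For k unaffected, independent dimensions, P(at least one false rejection) = 1 − 0.95^k:

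| k | probability |
|---|---|
| 1 | 5.0% |
| 2 | 9.8% |
| 4 | 18.5% |
| 7 | 30.2% |

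With k = 7 and test statistics correlated at 0.3, 0.5 or 0.7 (assumed), it is about 27%, 23% and 18%. The formula gives 33.7% for k = 8, but that is not an error rate of this procedure. With eight unaffected independent dimensions the composite is unaffected too, and the gate then caps the error at 5%.

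**3. Error of the whole procedure.** These simulations use 89 per arm, a control composite of 25%, and false claims counted only when step 1 is significant. Latent correlation between dimensions and the dimension-level rates are assumptions.

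*Several dimensions improved.* Control rates are equal across dimensions, latent correlation runs from 0 to 0.5, and the composite is raised to 45% or as near as the scenario allows (down to about 36%).

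| Dimensions improved | False claim, all trials | False claim, trials passing step 1 |
|---|---|---|
| 4 of 8 | 8–13% | 15–20% |
| 5 of 8 | 8–10% | about 11–13% |
| 6 of 8 | 6.5–7% | 8–9% |

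Separate simulations of the four- and five-dimension cases gave 7–14% of all trials. Only the all-trials column is a familywise error rate.

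*One dimension improved.* The result depends on how impaired that dimension is in the control group.
- Equal control rates: the composite barely moves, step 2 is seldom reached, and the rate is 3–4%.
- The improved dimension has a low control rate (45%) and carries the whole composite effect, dimensions independent: step 2 is reached in 79.7% of trials and the rate is 23.2%.
- The same at latent correlation 0.3, where the composite reaches only 41.5%: 17.5%.
- Latent correlation 0.5 (control rate again 45%) or 0.7 (control rate 35%), where the composite gains about 10 points: about 8.7%.

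**4. With a correction inside step 2.** Holm gives about 1–4% of all trials in the scenarios with several improved dimensions. In the 23.2% scenario it gives 3.0%, and Bonferroni at 0.05/8 = 0.00625 gives 2.8%.

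**The case against.** **The second endpoint is supportive.** The article says it lends credibility to the first, the sample size rests on the first alone, and no listed objective asks which dimension improves. It is true that the main conclusion is untouched. But the article also makes the second endpoint part of primary objective 1 and analyses it as confirmatory, so its error rate matters.

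**Eight tests is a reading.** The article never says eight tests, and 5% for the second endpoint could mean 5% for the endpoint as a whole. However, rates "separate for each dimension of the QoL profile 6 months after baseline" fit no single chi-square test of one rate, and the threshold p < 0.05 is set without any adjustment. A statistical analysis plan might add an order or a correction. Even then, the sentence in the article credits control to the two-step order alone, and that order does not provide it.

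**The size is driven by assumptions.** This stands. The 30% figure needs one dimension to carry the entire effect with seven independent unaffected ones. Under independence that dimension's control rate could be at most 0.25/0.45 = 55.6%. Control also holds when the first null hypothesis is true, and in some scenarios with a single improved dimension. None of this rescues the word used in the article, which claims control in every configuration.

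**Conclusion.** The concern holds. The two-step order does not give strong control of the familywise error at 0.05, because its second step is a family of eight tests at 5% each.

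The most useful figure is the 7–14% of all trials with a false confirmatory dimension claim when four or five of the eight dimensions improve. It rests on 89 evaluable patients per arm, equal control rates across dimensions and latent correlations of 0 to 0.5. Across all the scenarios examined the rate runs from 3–4% to 23%. The excess needs a true effect on the composite together with at least two unaffected dimensions.

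The test of the first primary endpoint, its 5% level and the 89 per group are sound on this point.

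**What to change.** Before database lock, make one of these changes in Statistical analyses, and carry it into the analysis plan:

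1. **Holm within step 2.** If the first null hypothesis is rejected, test the eight dimensions with Holm at a family level of 5%. The claim of a global alpha of 0.05 then holds whatever the correlation. Hochberg is a little more powerful but needs a condition on the dependence between tests.
2. **A fixed order.** List the eight dimensions in a stated order and stop at the first non-significant result. The section on the monitoring system says the dimensions were listed by importance after the preference experiments. Those were two separate experiments with six attributes each, so the eight-item order would have to be written out and justified.
3. **Descriptive reporting.** Report the eight rates with confidence intervals, drop the confirmatory label for the second endpoint, and delete the sentence on global alpha.

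The first option is the simplest that keeps the confirmatory aim. Its cost is some power for individual dimensions. No option changes the first endpoint, its power or the number of patients.

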### Study setting and eligibility criteria

Eight hospitals treating patients with lung cancer in Bavaria, Germany participate in patient recruitment. To achieve adequate participant enrolment there is regular contact between the study unit and the clinicians who are responsible for patient recruitment in the eight hospitals.

The following inclusion criteria apply: (1) primary diagnosis of lung cancer (C33/C34); (2) treatment at one of eight recruiting centres (University Hospital Regensburg, Hospital Barmherzige Brüder Regensburg, Hospital St. Maria Donaustauf, Hospital St. Elisabeth Straubing, Hospital Bayreuth, Sana Hospital Coburg, Hospital Kulmbach, Hospital Bamberg); (3) a time interval between the date of histology and the date of study entry not exceeding 6 months; (4) informed consent (a model consent form can be made available on request).

The exclusion criteria are as follows: (1) unavailability of a study clinician for patient recruitment (e.g., illness); (2) misclassification of the patient in the candidate list (e.g., no primary diagnosis, no lung tumour); (3) refusal of trial participation by the coordinating practitioner; (4) living outside the defined study region (Germany, Bavaria: Upper Palatinate, Lower Bavaria, Upper Franconia); (5) age under 18 years; (6) pregnancy/breastfeeding; (7) inability to fill out the QoL questionnaire (physical, psychological, cognitive, language reasons); (8) refusal of trial participation.

To ensure high external validity [22], there will be no exclusion of elderly patients or according to tumour stage or patient sex. Furthermore, no constraints will be made according to the type of therapy. However, these factors will be accounted for in the data analyses. External validity is also maintained by population-based inclusion of patients from urban and rural areas and by implementing the QoL monitoring system in routine follow-up care. The selection of study participants is shown in Fig. 1.

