### Randomisation and blindness

Subjects who meet inclusion criteria but none of the exclusion criteria are randomly assigned to the intervention or control group (1:1 allocation ratio) with the underlying parameters block randomisation and stratified randomisation with the strata gender (female/male) and centre. Random lists were generated by the Center for Clinical Studies (CCS) using the software SAS 9.4. Based on these random lists of digits, a coworker of the Tumor Center Regensburg (TCR), otherwise not involved in the trial, creates paper cards for each of the six recruiting centres specifying the study group for male and female participants and inserts them in serially numbered opaque, sealed envelopes. This stack of envelopes is kept in a locked safe at the study coordination unit of TCR, which is separated from the study research unit of UR/TCR in terms of space, organization and personnel to which only the two study coordinators have access. This procedure ensures that study coordinators who are responsible for randomisation of study patients are kept blind to the randomisation sequence. The eligibility of the study patients is determined by study clinicians in each of the six recruiting centres. If all criteria are fulfilled and the patient has given informed consent the study clinician sends the recruitment document to the study coordination unit (TCR) by fax. The exact date and time of fax entry determine the order in which patients from each centre are randomised.

The recruiting clinicians who determine study eligibility are blinded to the randomisation sequence. CPs and patients cannot be blinded to allocation for practical reasons because the intervention requires that intervention group patients and their CPs have access to the results of QoL monitoring. However, the study staff conducting the patient and physician evaluations after 3 and 6 months will be blinded to the condition of allocation.

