### Procedure

All participants (in the intervention and control groups) complete two QoL questionnaires (European Organisation for Research and Treatment of Cancer (EORTC) QLQ-C30 and QLQ-LC29 [30–32]) at the following time points: baseline (during the first 2 months of confirmed diagnosis of primary lung cancer) and 1, 2, 3, 4, 5, and 6 months after baseline (see. Figure 2). The first QoL measurement (baseline) takes place in the hospital by using a paper–pencil version of the QoL questionnaires for practical reasons. QoL data are entered manually into the online QoL monitoring system by a study coordinator at the study coordination unit so that patients and their CPs have online access to the results of the baseline QoL monitoring. All further QoL measures (1, 2, 3, 4, 5, and 6 months) will be completed on the patient`s mobile phone or computer via a secure web portal. For this purpose, after study entry each patient receives an email from the study coordination unit at the Tumor Center Regensburg with a link to activate the user account and assign a password. At 1, 2, 3, 4, 5, and 6 months after baseline each patient receives an email with a link to the QoL measurement, which is valid for two weeks. Patients who have not completed their QoL monitoring will receive two email reminders (after seven days and after 12 days). Once a QoL measurement has been completed it can no longer be edited. If participants have missed two QoL measurements in a row or if the QoL measurement at 6 months (primary endpoint) is missing they will be contacted by phone by one of the two study coordinators of the study coordination unit to check if there are any difficulties (e.g., use of the web application, internet access). If a participant has no regular access to the internet, there is also the possibility of a paper-based QoL measurement. For this purpose, QoL questionnaires are sent to the patient`s home by post at each timepoint for QoL measurement including a stamped return envelope.

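### The confirmatory chi-square test is valid and delivers its planned power, but it leaves out the randomisation strata and baseline QoL and so gives up efficiency, nearly all of it through baseline QoL

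*Protocol article*

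**What the plan says.** Under Randomisation and blindness, allocation uses "block randomisation and stratified randomisation with the strata gender (female/male) and centre". Under Procedure, "All participants (in the intervention and control groups) complete two QoL questionnaires" at baseline and monthly to month 6, so each patient has a starting value on the scales that later define response.

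Under Statistical analyses, "The analyses of the primary endpoints (including both the first and second primary endpoints) will be conducted using the" chi-square test of independence at p < 0.05. The second endpoint is confirmatory only if the first is significant. Adjustment appears in two other places in that section:

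- a multivariable regression, labelled a sensitivity analysis, whose covariates are described only as possible risk factors;
- secondary ANCOVAs of continuous QoL with "sex, age, study region, and baseline QoL as covariates".

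Centre, a stratification factor, is named as a covariate in no analysis. The Sample size section is built on the same chi-square test: 25% against 45% responders, 89 per group, 110 randomised per group.

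**The concern.** A primary analysis normally reflects the factors used to restrict the randomisation and uses a strong baseline predictor when one is measured in everyone. Here it does neither.

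The responder endpoint is month-6 status on all eight scales, whatever the starting level. Tumour stage and type of therapy are not restricted at entry, so starting levels will plausibly differ widely between patients. Some of the variation in month-6 response is then predictable from baseline, and the chi-square test treats it all as noise.

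The first endpoint is also the gate to the second, so any power forgone on the first carries over to the confirmatory status of the second.

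**Working it through.** **1. The plan's own figure.** Inputs from the Sample size section: p₀ = 0.25, p₁ = 0.45, α = 5% (taken as two-sided), power 80%, 1:1 allocation.

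n = [z₀.₉₇₅·√(2p̄q̄) + z₀.₈₀·√(p₀q₀ + p₁q₁)]² / (p₁ − p₀)², with p̄ = 0.35

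= [1.960·√0.455 + 0.842·√0.435]² / 0.04 = (1.322 + 0.555)² / 0.04 ≈ 88.1, rounded up to **89**.

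This matches the protocol. Power at 89 per arm is 80.4%. With 20% loss from 110, 110 × 0.8 = 88 per arm remain, and power is 80.0%. Test and sample size agree.

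**2. Simulation set-up.** 220 patients, 8 centres × 2 sexes, 20% random dropout, marginal response rates held at 25% and 45% (25% in both arms under the null), 4,000 trials per scenario. Assumptions that are not in the protocol: block size 4, and the prognostic strength of centre, sex and baseline. Monte Carlo standard error is √(0.05 × 0.95 / 4000) ≈ 0.35 points for a 5% rejection rate and √(0.8 × 0.2 / 4000) ≈ 0.63 points for 80% power.

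**3. Effect of ignoring the strata alone.** The comparison is with a Cochran–Mantel–Haenszel (CMH) test stratified by sex × centre.

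| Strata effect (centre SD; sex ±, log-odds) | Chi-square, null | Chi-square, power | CMH, power |
|---|---|---|---|
| none | 5.4% | 80.0% | 79.0% |
| 0.3; 0.2 | 5.2% | 80.2% | 80.0% |
| 0.5; 0.3 | 4.5% | 80.4% | 81.4% |
| 0.8; 0.4 | 3.8% | 81.0% | 84.4% |

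Stratifying moves power by about −1 to +3 points. The chi-square test becomes conservative only as the strata become strongly prognostic. The mechanism is that stratified allocation removes part of the between-stratum variation from the treatment difference, while the chi-square variance still counts it.

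**4. Effect of ignoring baseline QoL.** The comparison is with a standardised risk difference from a logistic model with arm, sex and a continuous baseline score (centre not in the model).

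| Baseline effect (log-odds per SD) | Chi-square, power | Adjusted, power | Gain | Adjusted, null |
|---|---|---|---|---|
| 1.0 | 79.9% | 87.0% | 7.1 | 5.1% |
| 1.5 | 80.0% | 90.6% | 10.6 | 5.6% |
| 2.0 | 80.8% | 94.3% | 13.5 | 5.9% |

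The last row is slightly flattered by its null rejection rate, so it is left out of the headline range. In these three scenarios the chi-square test rejected under the null in 4.5–5.0% of trials.

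A separate simulation at 89 per arm, with baseline effects of 0.7–1.5 log-odds per SD, gave about 81% power unadjusted and 83–91% adjusted. A model with sex, region and baseline had null rejection of 4.9–5.7%.

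**5. Is a fully stratified model feasible?** The eligibility section states "Eight hospitals treating patients with lung cancer in Bavaria, Germany participate in patient recruitment", while the randomisation section has a coworker who "creates paper cards for each of the six recruiting centres". That means 8 × 2 = 16 or 6 × 2 = 12 strata. With 2 × 89 = 178 evaluable patients, the average is 178/16 ≈ 11 or 178/12 ≈ 15 per stratum. Under the null about 178 × 0.25 ≈ 45 patients respond. In a simulation of a logistic likelihood-ratio test with every centre as its own term plus sex and baseline, null rejection was 5.7–6.3%, against 4.3–5.4% for the chi-square test.

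**The case against.** The strongest defence is that nothing is broken. The sample size was computed for this very test and reproduces exactly, so the trial has the power it claims at 89 evaluable per arm. A chi-square test needs no model and no pooling rule. The benefit of adjustment depends on a correlation that the protocol does not report. The planned sensitivity regression could already contain baseline QoL, centre and stage, since its covariates are not listed, and such a list is commonly left to an analysis plan. All of this stands. It makes the point one of efficiency, not validity. It does not remove it, because a sensitivity analysis does not decide the trial, and the protocol itself fixes the deciding test as unadjusted.

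A reader might infer more than the text supports:

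- *That ignoring the strata distorts the error rate in a harmful way.* It does not. Departures from 5% are on the conservative side and are small unless the strata are strongly prognostic.
- *That the choice of test leaves the trial below its target power.* The protocol's own inputs do not show this. What is lost is power above the stated target.
- *That tumour stage is promised and then dropped.* The eligibility section says of stage, age, sex and therapy type: "However, these factors will be accounted for in the data analyses". The sensitivity regression is a natural place for them, so no contradiction is shown.
- *That using study region in place of centre in the ANCOVA is an error.* It is a coarser grouping in a secondary analysis, and a defensible trade-off when centres are small.

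**Conclusion.** The point holds as a recommended improvement to a valid test. Adjusting the primary analysis for baseline QoL would raise power from about 80% to roughly 83–91%, for an assumed baseline effect of 0.7–1.5 log-odds per SD. If baseline turned out to be weakly prognostic, the gain would be smaller. The strata matter little for power (about −1 to +3 points); including them is mainly a matter of matching the analysis to the randomisation. The results rest on simulation with assumed prognostic strength, an assumed block size of 4 and dropout at random.

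**What to change.** For the first endpoint, make the primary analysis a prespecified logistic regression with arm, sex, centre and baseline QoL (baseline responder status or a baseline profile score, chosen in advance). Pool small centres within region by a rule written down beforehand. Report the standardised risk difference with a robust 95% confidence interval and the matching test; this stays on the same marginal scale as the 25% against 45% of the sample size. For the second endpoint, use the same model with that dimension's own baseline score. Keep the chi-square test as a supportive analysis. Reconcile six and eight centres first, because the pooling rule depends on it.

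The cost is wording in the protocol and analysis plan, fixed before outcomes are seen by arm; every variable is already collected. There are two downsides. A pooling threshold has to be chosen, and type I error may run slightly above 5% if too many centre terms are kept, which is the reason for pooling. The chosen model's null rejection rate should be checked by simulation before it is fixed.
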